### Data analysis

The primary analysis will compare the outcome measures between the intervention and control groups by following the intention-to-treat principle. Additionally, per-protocol analyses will also be conducted. All analyses will be done through SPSS V29 or SAS 9.4. A two-sided p-value below 0.05 will be deemed statistically significant. Results will be reported according to the Consolidated Standards of Reporting Trials (CONSORT) statement regarding eHealth [73]. The statistician in charge of the final analysis will be blinded to group allocation to minimise bias. Repeated measures ANOVA analyses will be done to evaluate differences between the two groups over time. In the case of multiple comparisons, Bonferroni adjustment of p-values will be applied to avoid over-interpretation of the results. Effect size (i.e., Cohen’s d) will also be calculated. For the qualitative data, the interviews will be audio-recorded and transcribed before the analysis. Data analysis will be conducted using thematic analysis as informed by Braun and Clarke [74], where key themes will be identified and refined. A codebook will also be developed to serve as a coding framework for coding of the transcripts. Data management and qualitative analysis will be done through NVivo V11.

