**Methods:**

A pilot two-armed randomised controlled trial will be conducted on 60 informal caregivers of PWD recruited via convenience and snowball sampling. Thirty participants will be assigned to the intervention group, while another 30 will be in a waiting-list control group. Questionnaires will be administered at baseline and one month after, with the primary outcome being the difference in the change of depressive symptoms among the two groups.

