**Statistical analysis:**

Primary analyses will follow the intention-to-treat principle and compare changes from baseline to the one-month follow-up time point relative to the control group. A repeated measures ANOVA will be conducted to examine differences between the groups over time.

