## Methods

### Study design

A pilot two-armed randomized control trial (RCT) design will be adopted to test the effectiveness of the *Kampung Care* app (*Kampung Care* is a local expression of a caring community). Sixty eligible caregivers of PWD will be enrolled in the RCT and randomly allocated to either the intervention or control group. No blinding will be used as participants and study team members need to be aware of which group the participant belongs to in order to start the intervention. Participants in the intervention group will use the app for one month, while those in the control group will be on a waiting list for one month. Outcome measures will be assessed at baseline and one-month after the baseline assessment (post-assessment). Thereafter, qualitative interviews will be conducted with participants from the intervention group to gather feedback on their experience with the app and areas for improvement. The Standard Protocol Items: Recommendations for Interventional Trials (SPIRIT) checklist is provided (see S1 File).

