### Sample size

Given that this is a pilot RCT with the primary aim of assessing the feasibility and potential effectiveness of the ’Kampung Care’ mobile intervention, we followed the recommendation from a methodological study that a sample size of 25 per intervention arm is required if the main study is designed with 90% power and two-sided 5% significance for an intervention with a small effect size [39]. No formula or software was used in the calculation. With a 1:1 allocation ratio, the required sample size was determined to be 50. As mobile-based intervention studies tend to have high attrition rates, we doubled our preliminary sample size to 100 to ensure there will be a sufficient sample for analysis. However, following the initial recruitment, we found the attrition rate among our target group to be quite low and thus adjusted our final sample to 60 –with 30 participants randomly allocated to the intervention group and waitlist control group respectively. For the in-depth interview, we intend to recruit up to 20 participants from the intervention group. This is from an experiential perspective. However, the final sample will depend on data saturation–the point at which no new information is being observed and collected to form distinct themes.

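### With two time points the planned repeated measures ANOVA is a change-score t-test, and adjusting for the baseline CES-D already collected would be more precise at no cost

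*Protocol article*

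**What the plan says.** The Methods paragraph of the Abstract sets the target, "with the primary outcome being the difference in the change of depressive symptoms among the two groups". The Abstract's statistical paragraph adds: "Primary analyses will follow the intention-to-treat principle and compare changes from baseline to the one-month follow-up time point relative to the control group". The Data analysis section repeats the intention-to-treat commitment ("The primary analysis will compare the outcome measures between the intervention and control groups by following the intention-to-treat principle") and then names the method: "Repeated measures ANOVA analyses will be done to evaluate differences between the two groups over time".

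Study design and Outcomes give two assessments, baseline and one month. Sample size sets 30 per arm. For software, "All analyses will be done through SPSS V29 or SAS 9.4"; no procedure is named. The article mentions neither a baseline-adjusted model nor a mixed model.

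**The concern.** With only one baseline and one follow-up score, a repeated measures ANOVA adds nothing to a comparison of mean change. Subtracting the whole baseline score is the best adjustment only when the follow-up score tracks baseline one for one. When the correlation is lower, subtraction over-corrects and adds noise. A trial of 60 people that applies a 5% two-sided test to a depression score can ill afford that, since the baseline CES-D is already in hand.

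The second, conditional issue is missing one-month scores. A change score needs both values. If the ANOVA is fitted by a routine that requires complete pairs, the analysis covers completers only. Change depends on baseline, so a loss related to baseline in one arm would shift the contrast.

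**Working it through.** **The plan's own figure.** Sample size takes 25 per arm from a methodological recommendation: 25 × 2 = 50, as stated. The final 60 leaves 50 after a loss of 10/60 = 16.7%. No power formula was used, so there is no stated power to reproduce.

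**Inputs.** From the article: two time points, 30 per arm, two-sided 5%. Assumed, because the article gives no figure: equal SD at both times (set to 1), correlation rho, a true difference of 0.5 SD, and the dropout rates.

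**Step 1: equivalence.** The group-by-time contrast is (post − baseline in the app arm) minus (post − baseline in the control arm), which is the difference in mean change. Its error mean square is half the pooled variance of the change scores, so F = t². On one simulated data set of 30 + 30, both came to 1.1900.

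**Step 2: variance.** In units of 2·SD²/n, the change score has variance 2(1 − rho) and the baseline-adjusted difference has 1 − rho². The ratio, adjusted over change, is (1 − rho²)/[2(1 − rho)] = (1 + rho)/2. Its inverse, 2/(1 + rho), gives the extra participants that the change score needs for equal precision.

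**Step 3: power.** Noncentral t with 58 df and noncentrality 0.5/√(2v/30), where v is the variance term from step 2. For rho = 0.5, change: 0.5/√(2 × 1.0/30) = 1.936, power 47.8%. Adjusted: 0.5/√(2 × 0.75/30) = 2.236, power 59.4%. Losing one df for the covariate changes this by less than 0.1 percentage point.

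| rho | variance ratio | extra n for change score | power, change | power, adjusted |
|---|---|---|---|---|
| 0.5 | 0.75 | 33% | 48% | 59% |
| 0.6 | 0.80 | 25% | 57% | 66% |
| 0.7 | 0.85 | 18% | 69% | 76% |
| 0.8 | 0.90 | 11% | 85% | 89% |
| 0.9 | 0.95 | 5% | 98.9% | 99.2% |

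At rho = 0.5 the change score has variance 2(1 − 0.5) = 1, the same as comparing one-month scores and ignoring baseline altogether.

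**Step 4: missing one-month scores, if pairs are required.** Suppose dropout in one arm follows a logistic model with slope 1 per SD of baseline, and loss in the other arm is unrelated to baseline. If m is the mean standardised baseline of the completers in the first arm, the change contrast is biased by −(1 − rho)·m. The baseline-adjusted contrast is unbiased when the regression is linear.

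| loss in that arm | m | bias at rho 0.5 | at 0.6 | at 0.7 |
|---|---|---|---|---|
| 5% | −0.047 | 0.024 SD | 0.019 | 0.014 |
| 10% | −0.091 | 0.045 | 0.036 | 0.027 |
| 17% | −0.149 | 0.074 | 0.060 | 0.045 |

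For scale: at 17% loss about 25 per arm remain. The standard error of the change contrast is then √(2 × 1.0/25) = 0.283 at rho 0.5 and √(2 × 0.6/25) = 0.219 at rho 0.7, so the bias is 0.074/0.283 = 0.26 and 0.045/0.219 = 0.21 of a standard error.

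**The case against.** **The change-score test is valid, and this is a pilot.** Both are true. Under randomisation with complete data the planned test is unbiased, and no promised power is missed because the sample size did not come from a power calculation. What remains is an efficiency argument. It still matters, because the article states an effectiveness aim, a primary outcome and a significance threshold.

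**The primary outcome is defined as change.** It can stay so. Regressing change on group and baseline gives the same treatment coefficient as regressing the one-month score on them.

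**Rho and the effect size are assumed.** They are, and the gain shrinks as rho rises. Apart from one degree of freedom, the adjusted analysis does not lose precision at any rho below 1.

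**Stronger readings that the article does not support.**
- A reader might infer that the intention-to-treat promise is broken because people without a one-month score will be dropped. The article does not say so. It follows only if a classical routine needing complete pairs is used. The listed software can also fit likelihood-based models, and the approved full protocol and any SAP, which are not shown, may settle missing data.
- A reader might infer serious dropout bias. The 17% scenario is one assumption. Sample size reports low attrition so far, without a figure, and cut the target from 100 to 60 because of it; the Discussion lists high dropout only as a possibility. At 5% loss the bias is about 0.02 SD.
- A reader might object that the ANOVA's between-groups main effect averages baseline and follow-up and so halves the effect. The Abstract makes the comparison one of change, so the group-by-time contrast is plainly the one intended.

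**Conclusion.** The concern holds as a free improvement, not as an error that invalidates the analysis. The equivalence to a change-score t-test and the variance ratio (1 + rho)/2 are exact, given equal SDs at the two times. The practical size depends on a correlation that the article does not give. For an assumed 0.5 SD difference, the gain is 12 percentage points of power at rho 0.5 (47.8% to 59.4%), 7 at 0.7 (69.1% to 76.0%), 3 to 4 at 0.8 and almost nothing at 0.9. It exists even with no dropout.

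The missing-score point is secondary and conditional on two things: a routine that needs both scores, and loss that depends on baseline in one arm only. In those assumed scenarios the bias runs from about 0.02 SD at 5% loss to about 0.05–0.07 SD at 17%.

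**What to change.** In Data analysis, and to match in the Abstract, make the primary analysis a linear model of one-month CES-D (or its change) on group with baseline CES-D as covariate. Report the adjusted mean difference with its 95% confidence interval. Use the same model for each secondary scale with that scale's own baseline. Repeated measures ANOVA can stay as a supporting analysis.

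This model also needs a one-month score, so on its own it does not retain people who lack one. To include every randomised participant with any score, state a likelihood-based mixed model. Two cautions apply:
- With baseline means left free in each arm and complete data, the mixed model's group-by-time contrast is again the difference in mean change. It then addresses missing scores but not precision.
- Constraining the baseline means to be equal recovers the precision. However, Study procedure and the Fig 1 legend place the baseline assessment after allocation, and Study design says participants are not blinded. Equal baseline means are therefore not guaranteed by design, and the plan should say so if it uses the constraint. The same ordering can also distort a change score, so it is no reason to keep the current method.

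The cost is analysis wording only. No new data are needed, the sample size is unaffected, and both listed packages fit these models.

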### Outcomes

Assessments to examine caregiver outcomes will be conducted at baseline and one month after baseline (post-assessment) for both the intervention and control groups. These will be conducted in English either online via videoconferencing or face-to-face at a location preferred by the participants.

The English version of the following questionnaires will be used in our study:

Centre for Epidemiological Studies-Depression (CES-D) ScaleGeneralized Anxiety Disorder– 7 item scaleZarit Burden InterviewRevised Scale for Caregiving Self-efficacyDementia Knowledge Assessment ScaleCoping Orientation to Problems ExperiencedPositive Aspects of Caregiving ScalePositive Mental Health instrument (short form)

The 20-item Centre for Epidemiological Study Scale (CES-D) will be used to measure the primary outcome–depressive symptoms amongst caregivers [50]. The instrument comprises 20 items, each rated on a 4-point Likert scale from 0 (*rarely or none of the time*) to 3 (*most or almost all the time*). The total score ranges from 0 to 60, with a score of 16 or higher indicating a risk for clinical depression [51]. The CES-D is a widely used scale which has been validated in Singapore [52] and was found to have an internal reliability of 0.91 when used in our previous study [25]. It also demonstrated good validity and reliability in detecting caregiver depression in another local study amongst caregivers of PWD [53]. Please see Table 1 for details on the secondary outcome measures.

**Table 1 pone.0305729.t001:** Measurement of secondary outcomes in the study.

Outcome	Questionnaire	Description
Anxiety	Generalized Anxiety Disorder– 7 item scale (GAD-7)	Each item of the Generalized Anxiety Disorder– 7 item scale (GAD-7) [54] is scored on a 4-point Likert scale from 0 (not at all) to 3 (nearly every day), with scores ranging from 0 to 21. A score of 10 or higher has been recommended as a cut-off point for identifying cases of GAD, while cut points of 5, 10, and 15 can be interpreted as mild, moderate, and severe levels of anxiety respectively [54]. The GAD-7 has been validated amongst the general population in Singapore [55] and used on a sample of local primary caregivers with a high internal consistency of 0.89 [56].

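### Free improvement: keep the CES-D test outside the multiplicity adjustment at two-sided 0.05, and replace Bonferroni by Holm for the seven secondary scales

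*Protocol article*

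**What the plan says.** The Abstract describes a single primary outcome, "with the primary outcome being the difference in the change of depressive symptoms among the two groups". The Outcomes section assigns it to the CES-D, which "will be used to measure the primary outcome–depressive symptoms amongst caregivers", and points to Table 1 for the rest: "Please see Table 1 for details on the secondary outcome measures". Table 1 lists seven instruments: GAD-7, Zarit Burden Interview, RSCSE, DKAS, brief COPE, PAC and short PMH.

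The Data analysis section does not mention the CES-D. It says "The primary analysis will compare the outcome measures between the intervention and control groups by following the intention-to-treat principle", then adds per-protocol analyses. It sets one threshold, "A two-sided p-value below 0.05 will be deemed statistically significant", and one model, "Repeated measures ANOVA analyses will be done to evaluate differences between the two groups over time". Multiplicity is handled in one conditional sentence, "In the case of multiple comparisons, Bonferroni adjustment of p-values will be applied to avoid over-interpretation of the results". Neither a family nor a number of tests is given.

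**The concern.** The Outcomes section separates one primary from seven secondary outcomes, but the multiplicity rule does not carry that separation over. A trial with one pre-named primary outcome, two arms and one post-baseline assessment needs no adjustment of its primary test. The rule does not say so, which leaves room to count the CES-D among eight comparisons. A CES-D p-value between 0.00625 and 0.05 would then be positive on one reading and negative on another.

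Separately, the section commits to Bonferroni by name. Holm controls the same familywise error under any dependence between the tests, rejects every hypothesis that Bonferroni rejects, and sometimes rejects more. In a trial of 60 people, the choice of Bonferroni gives up power on the secondary scales with nothing gained in error control.

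**Working it through.** **The plan's own figures.** The Sample size section takes 25 per arm from a cited recommendation, so 25 × 2 = 50. This was doubled to 100 and later set at 30 × 2 = 60. The 90% power quoted there ("a sample size of 25 per intervention arm is required if the main study is designed with 90% power and two-sided 5% significance") belongs to a later main study. No power is stated for this trial's CES-D test, so there is none to reproduce, and the effect sizes below are assumptions.

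**Inputs.** n = 30 per arm (Sample size); two-sided 0.05 (Data analysis); eight scales, CES-D plus seven (Outcomes, Table 1). Assumed: no dropout, one score tested per scale, and d = true between-group difference in change divided by the SD of change.

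**Step 1: the test.** With two groups and two time points, the group-by-time test in a repeated measures ANOVA is equivalent to a two-sample t test on change, with df = 2 × 30 − 2 = 58 and noncentrality d × √(30/2) = 3.873d. That is 1.94 at d = 0.5 and 3.10 at d = 0.8. Power is the probability that a noncentral t variable falls outside ± the critical value.

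**Step 2: CES-D inside or outside an eight-test Bonferroni family.** The thresholds are 0.05 and 0.05/8 = 0.00625.

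| d | power at 0.05 | power at 0.00625 | share kept |
|---|---|---|---|
| 0.2 | 0.119 | 0.024 | 20% |
| 0.3 | 0.208 | 0.054 | 26% |
| 0.5 | 0.478 | 0.195 | 41% |
| 0.6 | 0.628 | 0.314 | 50% |
| 0.8 | 0.861 | 0.604 | 70% |
| 1.0 | 0.968 | 0.844 | 87% |

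Power more than halves only for d below about 0.60. If Bonferroni covers only the seven secondary scales, the CES-D keeps 0.05 and loses nothing.

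**Step 3: Bonferroni against Holm on the seven secondary scales.** Bonferroni compares every p-value with 0.05/7 = 0.00714. Holm compares the ordered p-values with 0.05/7, 0.05/6, …, 0.05/1, that is 0.00714, 0.00833, 0.0100, 0.0125, 0.0167, 0.025 and 0.05, and stops at the first failure. I simulated 40,000 trials per setting with 30 per arm, normal change scores, and the same d on all seven scales.

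| d | correlation between scales | Bonferroni, average power per scale | Holm, average power per scale |
|---|---|---|---|
| 0.5 | 0 | 20.7% | 23.3% |
| 0.5 | 0.2 | 20.8% | 24.5% |
| 0.5 | 0.4 | 20.8% | 25.3% |
| 0.8 | 0 | 62.2% | 76.1% |
| 0.8 | 0.2 | 62.2% | 75.3% |
| 0.8 | 0.4 | 62.3% | 74.4% |

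The exact t calculation gives 20.8% and 62.2% for Bonferroni, which agrees. With no true effect on any scale, both methods gave at least one rejection in the same share of trials (4.6% to 4.8%). Holm rejected everything that Bonferroni rejected in every simulated trial.

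**The case against.** A reader might infer that the article makes all eight instruments primary and so tests the CES-D at 0.05/8. The text does not support this. The Abstract and the Outcomes section name one primary outcome. The phrase about the primary analysis is followed at once by the per-protocol analyses, so it most naturally names the analysis set rather than an outcome hierarchy. The Bonferroni sentence is conditional, the section sets 0.05, and neither eight tests nor 0.00625 appears anywhere. The reading that best fits the rest of the article is that the CES-D is tested at 0.05 and adjustment applies elsewhere.

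A reader might also fear eight unadjusted tests, with a chance of at least one false positive of 1 − 0.95⁸ = 34%. That figure needs Bonferroni never to be applied, needs independent tests, and ignores the sentence that prescribes an adjustment.

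Nor must the family consist of eight scales. The closing paragraph of the Background also plans before-and-after comparisons, and several instruments have subscales (the brief COPE has 14 domains), so Bonferroni may be meant for any of these. The family may well be defined in the full protocol or analysis plan. Its absence from a condensed article is not in itself a fault. Bonferroni is also a valid method.

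All of this stands. It leaves the narrower point untouched: the method named in the article is Bonferroni, and Holm does at least as well whichever family was meant.

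**Conclusion.** This is a worthwhile improvement at almost no cost, not an error that invalidates the analysis. The article fixes Bonferroni without placing the single primary outcome outside it, and Bonferroni is never more powerful than Holm at the same familywise error.

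The loss for the CES-D (48% to 20% at 0.5 SD, 86% to 60% at 0.8 SD) arises only under one possible reading, with a family of eight, 30 per arm and no dropout. A loss of more than half needs a true effect below about 0.6 SD. The gain from Holm (about 21% to 23–25%, and about 62% to 74–76%) assumes that all seven secondary scales share the same true effect and is a favourable case. If only one scale is affected, the gain is close to nil, but it is never negative. As the trial is a pilot, what is at stake is the clarity of its significance claims.

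**What to change.** In the Data analysis section, replace the Bonferroni sentence with two sentences to this effect: the between-group difference in change in CES-D from baseline to one month is the sole primary test, at two-sided 0.05 without adjustment; the seven secondary scales, one pre-named score each, form one family tested with Holm's procedure at familywise 0.05.

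Record and date the change before the analysing statistician has outcome data by arm. Align the full protocol and any analysis plan if they name Bonferroni. How subscales are reported is a matter of preference and need not be changed for this point.

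The cost is two sentences, with no added participants, data or software. Holm-adjusted p-values can be computed by hand. One small trade-off is that Holm has no simultaneous confidence intervals as simple as Bonferroni's; the article promises adjusted p-values and effect sizes, not such intervals.

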## Discussion

To the best of our knowledge, this study is the first in Singapore which will assess the feasibility and effectiveness of an app-based intervention for the mental health of informal caregivers of PWD. Despite a prevalent culture of digital usage and positive sentiments towards digital technologies in Singapore [28], mobile-based interventions to support dementia caregivers in the local setting remain scarce, not to mention ones that can target the multifaceted needs of caregivers of PWD. To maximise the feasibility and effectiveness of the app for caregivers, we drew on findings from our past studies [25, 29, 42–45] to ensure a user-centered app designed to address the experiences and needs of local caregivers. Our study can provide valuable insights which will contribute to the evidence base for the effectiveness of apps like *Kampung Care* in promoting the mental well-being of caregivers of PWD in Singapore.

Nevertheless, we foresee a few limitations of this study. The use of convenience sampling may render potential biases in the dataset, which calls for caution in over-generalising the results. Moreover, this study requires participants to be adept at using mobile applications, which may be a barrier for seniors or individuals who are less digitally literate to participate. As a result, the sample may not be representative of the mainstream population of informal caregivers of PWD. Another possible limitation of this study is a high dropout rate, but strategies to overcome this include weekly reminders to motivate participants to use the app and offering an inconvenience fee after each assessment as an incentive. Notwithstanding these limitations, the proposed *Kampung Care* app is an innovative intervention which could inform and encourage the future design and evaluation of app-based interventions to the mental well-being of local dementia caregivers.

